**Inclusion Criteria**	
Adults (age greater than or equal to 18 years old)	
Diagnosis of Multiple Sclerosis	
Lower urinary tract symptoms (urinary frequency, urgency and/or incontinence)	
Failed prior first and second line therapy (behavioral and pharmacotherapy)	
Electing for Posterior Tibial Nerve Stimulation therapy for urinary symptoms. Patients performing Intermittent Catheterization are Eligible	

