**Exclusion Criteria**	
Age less than 18 years	
Indwelling catheters (urethral or suprapubic)	
currently pregnant or planning pregnancy	
Unable to attend weekly office visits for PTNS	
urodynamic findings of bladder outlet obstruction	
History of:	
bladder reconstruction (augmentation cystoplasty, catheterizable channel)	
cystectomy	
bladder stones	
pacemaker or defibrillator	
malignancy of bladder	
sacral neuromodulation	
intravesical injection of onabotulinum toxin within 9 months	

The PTNS procedure will be performed per the manufacturer’s specifications using a Neuromodulation System (Urgent® PC, Minnetonka, MN), as previously described [15]. Participants will undergo treatment for 30 min, once per week for 12 weeks. After 12 weeks, those with more than 50% improvement in symptoms based on a visual analog scale, will be offered maintenance PTNS sessions for 30 min every 28 days for a total of 24 months.

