### Study measurements

Eligible persons will be evaluated at baseline (time of first PTNS treatment) and then at months 3, 12 and 24 from baseline (Table 3). Patients will be administered instruments assessing LUTS, HRQOL, Bowel and Sexual symptoms. Data collection instruments are summarized in Table 4.

**Table 4 Tab4:** Description of data collection instruments

	Name	Description
**Urinary Measures**	3-day Voiding Diary	Patient completed 3 day assessment of fluid intake, output, incontinence episodes and pad changes.
	American Urological Association Symptom Score (AUA-SS)	Validated symptom score for the evaluation of Lower Urinary Tract Symptoms in Benign Prostatic Hyperplasia. Has been used in MS related research in the past.
	Michigan Incontinence Symptom Score (M-ISI)	Validated score developed to discern between type of incontinence and the severity and bother caused by urinary incontinence
	Neurogenic Bladder Symptom Score (NBSS)	Objective and validated assessment of bladder symptoms specifically created for use in patients with neurogenic bladder
**Bowel and Sexual Measures**	Sexual Satisfaction Scale	Validated, 5 item index addressing overall sexual adjustment in patients with MS and was adapted by the MSQLI from the Sexual History Form, scores range from 4 to 24 with higher scores indicating greater problems with sexual satisfaction.
	Bowel Control Scale	validated, 5 item scale evaluating constipation, bowel accidents, bowel urgency and the impact of bowel symptoms of lifestyle on a 25 point scale with higher scores indicating greater bowel problems
**General HRQOL**	SF-12	Validated 12 item quality of life survey for use in patients with chronic conditions.
**MS Impact**	Expanded Disability Scale	Physician Completed assessment of impact of MS

*HRQOL* Health Related Quality of Life. *MS* Multiple Sclerosis

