### Study outcomes

The primary outcome will be change in the median number of urinary frequency and urinary incontinence episodes on a 3-day voiding diary [37]. Secondary outcomes will be change in AUA symptom score (AUA-SS) and bothersome score, Michigan Incontinence Symptom Index (M-ISI), Neurogenic Bladder Symptom Score (NBSS), and from the Multiple Sclerosis Quality of Life Index (MSQLI) the Health Status Questionnaire (SF-12), Sexual Satisfaction Scale (SSS), and Bowel Control Scale (BCS) [28, 30–33].

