## Statistical analysis

Baseline descriptive demographic data will be presented for the entire cohort. The primary outcome of median number of urinary frequency and incontinence episodes on a 3-day voiding diary at 3, 12 and 24 months will be compared to baseline for each patient using paired analysis. Secondary outcome measures including total AUA-SS, M-ISI, NBSS, SF-12, SSS and BCS scores at 3, 12 and 24 months will be compared to baseline for each patient using paired analysis. Continuous variables will be evaluated using paired t-test and categorical data will be analyzed using McNemar’s test. Paired data will be evaluated using a 2-sided paired t-test. Median values will be analyzed using a Wilcoxon signed rank test. Statistical significance will be considered with *p* < 0.05.

In order to assess for predictors of improvement of symptoms response to PTNS, planned subgroup analysis will be performed stratifying patients based on gender, EDSS score, and burden of disease on MRI. Furthermore, an interim analysis at evaluating outcomes at 3 and 12 months after PTNS is planned.

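### The primary incontinence median is taken over patients who may have no leakage at baseline, so the reported change shrinks towards zero by an unknown amount

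*Protocol article*

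**What the plan says.** The inclusion criteria in Table 2 ask for "Lower urinary tract symptoms (urinary frequency, urgency and/or incontinence", so any one of the three symptoms is enough, and no minimum diary count is set. The narrative under Study design and population lists the three symptoms without the and/or, but refers to Table 2 for the full criteria. Table 2 adds that "Patients performing Intermittent Catheterization are Eligible"; among catheter users, only those with indwelling catheters are excluded.

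Under Study outcomes: "The primary outcome will be change in the median number of urinary frequency and urinary incontinence episodes on a 3-day voiding diary". Under Statistical analysis, the counts at 3, 12 and 24 months "will be compared to baseline for each patient using paired analysis", and "Median values will be analyzed using a Wilcoxon signed rank test". Neither count is limited to patients who have the symptom at baseline. The planned subgroups come from "stratifying patients based on gender, EDSS score, and burden of disease on MRI"; continence at baseline and catheter use are not among them.

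Table 4 describes the diary as "Patient completed 3 day assessment of fluid intake, output, incontinence episodes and pad changes". The form itself is not shown.

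**The concern.** Eligibility and the primary outcome do not match for incontinence. A patient who enters with urgency or frequency alone starts at zero leaks and can only stay there or rise. A median is especially sensitive to such patients: once more than half the values are zero, it is zero whatever happens to the rest. The Sample size section calls the study descriptive, so the estimated change and its interval are its main product. A small or zero median change could be read as little effect on leakage when it partly reflects how many patients had no leakage to lose.

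There is a lesser question for frequency. Intermittent catheterizers are expressly eligible, and their number of bladder emptyings may not carry the same meaning as a spontaneous voider's.

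**Working it through.** **Inputs from the article.** At least 50 enrolled, up to 10% dropout, so 50 × 0.9 = 45 evaluable; illustrative SD of the difference 3; target interval within ±1 (one third of an SD).

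**Inputs assumed.** The share dry at baseline, the leak rate and the size of benefit are not in the article. Dry patients are held at 0.

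**Step 1: the article's own precision figure.** The 95% half-width is t(0.975, n-1) × SD / √n. For n = 45 this is 2.015 × 3 / √45 = 0.90, inside ±1. The stated 95% chance of reaching ±1 comes out as 95.8% with 50 analysed and 86.0% with 45. That shortfall is a separate matter, and nothing below relies on it.

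**Step 2: precision among patients who can improve.** Same formula, with n = 45 × (1 - dry share), rounded down to whole patients.

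| Dry share (assumed) | Incontinent at baseline | Half-width at SD 3 |
|---|---|---|
| 0% | 45 | 0.90 |
| 20% | 36 | 1.02 |
| 30% | 31 | 1.10 |
| 40% | 27 | 1.19 |
| 50% | 22 | 1.33 |
| 60% | 18 | 1.49 |

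At 20% dry: 2.030 × 3 / √36 = 1.02, so ±1 is already exceeded.

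**Step 3: the mean change.** Cohort mean = (1 - dry share) × mean change in leaking patients. If leaking patients fall from 6 to 3 per 3 days, this is -3.0, -2.4, -2.1, -1.8 and -1.5 at 0, 20, 30, 40 and 50% dry.

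**Step 4: the median change.** The wording allows two readings, the change in the cohort median or the median of paired changes. Two simulated scenarios, each with 45 patients:

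*A. Leak rates vary widely between patients* (gamma-Poisson, shape 1.5, mean 6, rate ratio 0.6). The mean change in leaking patients is 6 × (0.6 - 1) = -2.4 throughout.

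| Dry share | Change in cohort median | Median of paired changes |
|---|---|---|
| 0% | -1.9 | -1.7 |
| 25% | -1.3 | -0.6 |
| 40% | -0.7 | -0.1 |
| 50% | -0.2 | 0.0 |

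The median of paired changes is exactly 0 in 48 to 49% of cohorts at 25% dry and in 88 to 91% at 40% dry (ranges over repeated runs).

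*B. Little variation between patients* (Poisson, 6 falling to 3).

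| Dry share | Change in cohort median | Median of paired changes |
|---|---|---|
| 0% | -3.0 | -2.9 |
| 20% | -2.8 | -2.0 |
| 30% | -2.5 | -1.2 |
| 40% | -2.3 | -0.4 |
| 50% | 0 | 0 |

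The shrinkage therefore depends on the spread of leak rates and on which median is meant. The end point does not: the median of 45 values is the 23rd in order, so with 23 patients dry throughout, every median is 0.

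**Step 5: the test.** In its usual form the signed-rank test drops zero changes, so patients who stay dry contribute nothing. In scenario A its whole-cohort power is about 98%, 95% and 89 to 91% at 25, 40 and 50% dry, against about 99%, 97% and 93 to 94% in leaking patients only.

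**The case against.** **Analysis sets are commonly left to the SAP or full protocol.** This is fair for the detail of the sets and for how a catheterization is logged, and no fault is claimed there. Who enters and what the primary count is are fixed in this article, however, and the mismatch lies between those two.

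**The whole cohort fits the descriptive aim.** This stands in part. The aim concerns patients treated for refractory LUTS, and new leakage over 24 months of a progressive disease is informative. The whole-cohort result should be kept; it is not sufficient alone.

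**A reader might infer that a real benefit would go undetected.** The documents do not support that. Under the stated signed-rank test, restricting to leaking patients gains only a few points of power even at 50% dry.

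**A reader might infer that the normality assumption in the Sample size section fails.** This was not shown. In scenario A, t-interval coverage for the mean change stayed at 94 to 96% at every dry share. A transformation cannot remove a cluster at zero, but coverage did not need one.

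**A reader might infer that catheterizers' frequency count does not measure symptoms.** That is an inference. The article gives no catheterization routine, does not say that these patients never void, and does not show the diary form. Their incontinence count remains usable.

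**Restricting has its own bias.** This stands. Selecting on at least one leak on the same diary that serves as comparator brings regression to the mean in a single-arm study. With no true effect, the spurious change is about -0.12 at a mean of 6 leaks (shape 1.5) and -0.27 to -0.45 at means of 3 to 1 (shape 0.5).

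**Conclusion.** The point holds as a low-cost improvement to how the primary incontinence result is estimated and reported. The mechanism follows from the article's own eligibility and outcome wording: dry patients are admitted, are counted, and cannot improve. The size rests on an unstated dry share and on assumed leak rates. It ranges from negligible when few are dry to a median change of 0 when just over half are dry and stay so. Nothing in the article suggests that half will be dry, so it would be wrong to say that the primary outcome cannot improve. What is affected is the median change and its precision, much more than the p-value. For catheterizers, the documents support only showing whether the frequency result depends on including them.

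**What to change.** 1. State that incontinence change is estimated in patients incontinent at baseline. Preferably identify them by a baseline measure other than the comparator diary; the M-ISI is already collected at month 0.
2. Show the whole-cohort result alongside, with the number of baseline-dry patients who develop leakage.
3. Give the number evaluable for the incontinence count and quote precision for that number, since ±1 at SD 3 no longer holds once about 20% of 45 are dry.
4. Say whether the reported figure is the change in medians or the median of paired changes.
5. Show the frequency result with and without intermittent catheterizers.

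Eligibility, treatment and visits are unchanged; the cost is some wording and a few tables. The downsides are fewer evaluable patients, a wider interval, and some regression to the mean if the baseline diary itself defines the subset, which should then be acknowledged. If the M-ISI defines it, a few patients may still record no leak on the baseline diary, and the same caution applies to M-ISI change within that subset.

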**Exclusion Criteria**	
Age less than 18 years	
Indwelling catheters (urethral or suprapubic)	
currently pregnant or planning pregnancy	
Unable to attend weekly office visits for PTNS	
urodynamic findings of bladder outlet obstruction	
History of:	
bladder reconstruction (augmentation cystoplasty, catheterizable channel)	
cystectomy	
bladder stones	
pacemaker or defibrillator	
malignancy of bladder	
sacral neuromodulation	
intravesical injection of onabotulinum toxin within 9 months	

The PTNS procedure will be performed per the manufacturer’s specifications using a Neuromodulation System (Urgent® PC, Minnetonka, MN), as previously described [15]. Participants will undergo treatment for 30 min, once per week for 12 weeks. After 12 weeks, those with more than 50% improvement in symptoms based on a visual analog scale, will be offered maintenance PTNS sessions for 30 min every 28 days for a total of 24 months.

### Recruitment

Participants will be recruited via a three-pronged approach. First, neurourology clinics at a tertiary care referral center will be screened for eligible patients. Eligible patients will be mailed letters regarding the study. Second, neurology and physical medicine and rehabilitation physicians at the same institution will be notified of the study. Finally, advertisements for the study will be posted on social media networks.

### Screening and enrollment

Patients who meet inclusion criteria will be evaluated at baseline. Demographic and social information, and complete history and physical and neurologic evaluation with the Expanded Disability Status Scale (EDSS) will be evaluated at this time. Information from prior brain and spine MRI studies will be collected, if available. Participants will complete baseline questionnaires outlined below and summarized in Table 3.

**Table 3 Tab3:** Outcome measurements and time points

	Time Points (month)			
	0*	3**	12	24
**Demographic Intake Form**	x			
**LUTS Measurements:**				
**3 Day Voiding Diary**	x	x	x	x
**AUA-SS**	x	x	x	x
**M-ISI**	x	x	x	x
**NBSS**	x	x	x	x
**Visual Analog Scale**		x		
**Sexual Satisfaction Scale**	x	x	x	x
**Bowel Control Scale**	x	x	x	x
**SF-12**	x	x	x	x
**Expanded Disability Scale**	x		x	x

*Time 0: start of PTNS therapy; **Time 3 months: end of weekly PTNS therapy; **AUA-SS* American Urological Association Symptom Score, *M-ISI* Michigan Incontinence Symptom Index, *NBSS* Neurogenic Bladder Symptom Score

### Follow-up and retention

Efforts will be made to follow-up all patients through 24 months after time 0 (initiation of PTNS). This is inclusive of patients who do not have an improvement of symptoms with initial 12 weeks of PTNS and do not pursue maintenance PTNS. In order to promote follow-up and retention, participants will be offered the opportunity to complete questionnaires in person or electronically, via a Research Electronic Data Capture (REDCap) [25]. Furthermore, participants will be compensated at the time of return of a 3-day voiding diary at times 0, 12, and 24 months.

### Collection of study data

Study data will be collected and managed using REDCap hosted at the University of Michigan [25]. REDCap is a secure, web-based application designed to support data capture for research studies [25].

### Study measurements

Eligible persons will be evaluated at baseline (time of first PTNS treatment) and then at months 3, 12 and 24 from baseline (Table 3). Patients will be administered instruments assessing LUTS, HRQOL, Bowel and Sexual symptoms. Data collection instruments are summarized in Table 4.

**Table 4 Tab4:** Description of data collection instruments

	Name	Description
**Urinary Measures**	3-day Voiding Diary	Patient completed 3 day assessment of fluid intake, output, incontinence episodes and pad changes.
	American Urological Association Symptom Score (AUA-SS)	Validated symptom score for the evaluation of Lower Urinary Tract Symptoms in Benign Prostatic Hyperplasia. Has been used in MS related research in the past.
	Michigan Incontinence Symptom Score (M-ISI)	Validated score developed to discern between type of incontinence and the severity and bother caused by urinary incontinence
	Neurogenic Bladder Symptom Score (NBSS)	Objective and validated assessment of bladder symptoms specifically created for use in patients with neurogenic bladder
**Bowel and Sexual Measures**	Sexual Satisfaction Scale	Validated, 5 item index addressing overall sexual adjustment in patients with MS and was adapted by the MSQLI from the Sexual History Form, scores range from 4 to 24 with higher scores indicating greater problems with sexual satisfaction.
	Bowel Control Scale	validated, 5 item scale evaluating constipation, bowel accidents, bowel urgency and the impact of bowel symptoms of lifestyle on a 25 point scale with higher scores indicating greater bowel problems
**General HRQOL**	SF-12	Validated 12 item quality of life survey for use in patients with chronic conditions.
**MS Impact**	Expanded Disability Scale	Physician Completed assessment of impact of MS

*HRQOL* Health Related Quality of Life. *MS* Multiple Sclerosis

#### Description of urinary symptom assessment tools

For evaluation of LUTS the following instruments will be utilized: 1) 3-day voiding diary, 2) American Urological Association Symptom Score (AUA-SS), 3) Michigan Incontinence Symptom Index (M-ISI), and 4) Neurogenic Bladder Symptom Score. Voiding diaries are recommended in the routine evaluation of patients with neurogenic overactive bladder and the 3 day diary has been shown to be reliable in the evaluation of urge urinary incontinence [26, 27]. The AUA-SS was validated in 1992 and has been widely used in urologic literature including in the assessment of patients with MS. [11, 28, 29] Scores range from 0 to 35 with greater scores indicating more severe symptoms. The M-ISI is a 10 item questionnaire was developed and validated to discern between type of incontinence and the severity and bother caused by incontinence [30]. Greater scores indicate increased symptoms and the minimally important difference for urge urinary incontinence subdomain is 2 points [30]. The M-ISI has been utilized in prior literature in the context of MS. [11] The Neurogenic Bladder Symptom Score is a 22 item survey developed and validated for use in patients with spinal cord injury, MS and spina bifida [31]. The NBSS is a symptom scale which captures data regarding urinary incontinence, storage and voiding symptoms and complications of neurogenic bladder [31]. (Table 4).

#### Description of adjunct assessment tools

Additional information regarding sexual activity and bowel symptoms will be assessed via selected tools which are part of the Multiple Sclerosis Quality of Life Index (MSQLI) [32, 33]. The MSQLI serves as a comprehensive assessment of HRQOL in patients with MS and consists of a Health Status Questionnaire (SF-36) and 9 subscales including bowel and sexual domains [32, 33]. For the purposes of this study the SF-12, Bowel Control Scale and Sexual Satisfaction Scale from the MSQLI are selectively utilized. The SF-12 is a 12-item version of the SF-36, the SF-12, was chosen to assess health status in order to decrease survey fatigue [34]. Literature has shown comparable results between SF-36 and SF-12 in the MS population [34, 35]. The Bowel Control Scale is a 5 item scale evaluating constipation, bowel accidents, bowel urgency and the impact of bowel symptoms of lifestyle on a 25 point scale with higher scores indicating greater bowel problems [33]. The Sexual Satisfaction Scale is a 5-item index addressing overall sexual adjustment in patients with MS and was adapted by the MSQLI from the Sexual History Form, scores range from 4 to 24 with higher scores indicating greater problems with sexual satisfaction [32, 33]. Both the Sexual Satisfaction Scale and the Bowel Control Scale have been widely used and validated as part of the MSQLI in the MS literature [32, 33]. (Table 4).

#### Description of neurologic disability assessment tools

Neurologic impact of multiple sclerosis in participants will be evaluated using the Expanded Disability Status Scale (EDSS) at baseline and annually by a neurologist, resulting in 3 measurements over the 24-month study time frame [36]. Additionally, we will evaluate participants for change in Magnetic Resonance Imaging (MRI) over the 24-month period, including T2 lesion number and location. The EDSS was developed in the 1950s and has long been the standard for assessing MS progression in phase III clinical trials [36]. The EDSS assesses eight neurological exam functional systems; EDSS 0 means normal and 10, death. Aside from EDSS, MRI will provide objective measures of MS disease burden as reflected on T2 lesion load (Table 4).

### Study outcomes

The primary outcome will be change in the median number of urinary frequency and urinary incontinence episodes on a 3-day voiding diary [37]. Secondary outcomes will be change in AUA symptom score (AUA-SS) and bothersome score, Michigan Incontinence Symptom Index (M-ISI), Neurogenic Bladder Symptom Score (NBSS), and from the Multiple Sclerosis Quality of Life Index (MSQLI) the Health Status Questionnaire (SF-12), Sexual Satisfaction Scale (SSS), and Bowel Control Scale (BCS) [28, 30–33].

### Sample size

In this descriptive study, we aim to enroll at least 50 participants. While it is likely that the count of episodes in each of the time frames follows a Poisson distribution, the difference statistic could very well be expected to follow a normal distribution. If not, appropriate transformations would be applied to create an approximately normal distribution. Allowing for up to a 10% dropout rate, this sample size will provide a 95% chance to have a 95% confidence interval for our change statistic that is within +/− 1/3 of a standard deviation. In other words, if we have an underlying standard deviation of 3 for the difference in counts, simulation results indicate that over 95% of the time, the 95% confidence interval for the change statistic would fall within the mean +/− 1. This will provide sufficient precision for our outcomes of interest.

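### The 95% assurance of a confidence interval within ±1/3 SD corresponds to about 50 evaluable patients; at the stated 10% dropout (45 evaluable) it is about 86%

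*Protocol article*

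**What the plan says.** The Sample size section describes the study as descriptive and sets a floor for recruitment: "we aim to enroll at least 50 participants". It then states what that number achieves: "Allowing for up to a 10% dropout rate, this sample size will provide a 95% chance to have a 95% confidence interval", the target being a "confidence interval for our change statistic that is within +/− 1/3 of a standard deviation". A worked example follows. It is conditional ("if we have an underlying standard deviation of 3 for the difference in counts") and reports that "simulation results indicate that over 95% of the time, the 95% confidence interval for the change statistic would fall within the mean +/− 1". The section treats the change as approximately normal ("the difference statistic could very well be expected to follow a normal distribution"), with a transformation if it is not, and concludes that the precision is sufficient. It gives no separate number of evaluable patients and no enrolment target above the floor of 50.

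The Statistical analysis section names the method: "Paired data will be evaluated using a 2-sided paired t-test". Wilcoxon signed rank tests are reserved for medians.

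**The concern.** The sentence makes the 95% assurance conditional on losing up to 10% of participants, so it should hold for as few as 45 patients with paired data. The chance that an interval is narrow enough depends on how variable the estimated SD is, and this chance changes quickly with sample size in the range 45 to 50. A figure that is right for 50 analysed patients is therefore visibly wrong for 45.

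This paragraph is the only justification of the study size. In a single-arm descriptive study, precision is the whole sizing criterion, so the figure should be correct under its own stated conditions.

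**Working it through.** **Inputs.** All come from the protocol article.
- Enrolled: 50. Dropout: up to 10%. Evaluable at the full allowance: 50 × 0.9 = 45 (Sample size).
- Confidence level 95%; target half-width 1/3 of the SD σ of the paired differences; claimed probability 95%, and more than 95% in the worked example (Sample size).
- σ = 3 in the example, so the target is 3/3 = 1 episode (Sample size).
- Approximately normal differences (Sample size) and a two-sided paired t-test (Statistical analysis), hence a t-interval for the mean change.

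**Formula.** The half-width is t·s/√n, where t is the 97.5% quantile on n − 1 degrees of freedom and s is the sample SD. Since (n − 1)s²/σ² is chi-square on n − 1 df,

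P(half-width ≤ σ/3) = P(χ² on n − 1 df ≤ n(n − 1)/(9t²)).

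σ cancels, so the result does not depend on the value 3.

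**Reproducing the plan's figure, n = 50.** t = 2.0096. The bound is 50 × 49/(9 × 2.0096²) = 67.41 on 49 df, giving **95.8%**. This agrees with the reported simulation result of over 95%.

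**Applying the stated dropout, n = 45.** t = 2.0154. The bound is 45 × 44/(9 × 2.0154²) = 54.16 on 44 df, giving **86.0%**. The chance of missing the target is about 14%, against the 5% implied.

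**Sensitivity of the result**

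| Evaluable n | t-interval | 1.96 in place of t |
|---|---|---|
| 45 | 86.0% | 91.3% |
| 48 | 92.9% | 96.0% |
| 49 | 94.5% | 97.0% |
| 50 | 95.8% | 97.8% |

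Other variants do not close the gap at 45:
- Simulated differences of Poisson counts with SD 3: about 85.4% at n = 45 and 95.4% to 95.6% at n = 50.
- Random (binomial) dropout at 10% from 50, instead of exactly 45 patients: 85.2%.
- Conditional on the interval covering the true mean: 85.5% at n = 45.

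**What 45 patients do assure at 95%.** Half-width = t·√(χ²₀.₉₅,₄₄/(44 × 45)) in units of σ. With χ²₀.₉₅,₄₄ = 60.48 this is 2.0154 × √(60.48/1980) = **0.352 SD**, or 3 × 0.352 = **1.06 episodes** at SD 3. The half-width at n = 45 when s equals σ is 2.0154/√45 = 0.300 SD.

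**The case against.** Several points count against making much of this.

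*The effect is small.* The half-width assured at 95% moves from 1.00 to 1.06 episodes in the plan's own example, and the typical half-width with 45 patients, about 0.30 SD, is still inside the target. No power claim depends on the figure. This stands, and it limits how serious the point is.

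*The plan says at least 50 and up to 10%.* Fewer losses or more enrolment would raise the probability; 48 evaluable patients give 92.9%. That is true, but the assurance is attached to 50 enrolled and is said to allow for the full 10%, so 45 is the case it has to cover.

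*The interval method is not stated in the Sample size section.* The t-interval is inferred from the paired t-test. The choice is reasonable but remains a choice. A multiplier of 1.96 gives 91.3% at 45, which is still short.

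*A looser reading might rescue the claim.* If the SD is treated as known, the half-width at n = 45 is a fixed 0.292 SD (1.96/√45) and no 95% chance arises. The point estimate falls within 1/3 SD of the true mean about 97.5% of the time at n = 45, but the text speaks of the confidence interval both times.

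A reader might also be tempted to go further than the document allows:
- That the worked example is badly false because the whole interval seldom lies inside the true mean ± 1. The text says only the mean. Read as the estimated mean, the sentence is a loose statement about half-width and is consistent with the one before it.
- That losses will be far above 10%, because some patients in a 12-month study in Table 1 did not enter maintenance. Not entering maintenance is not loss to follow-up here: the Follow-up and retention section intends to follow such patients to 24 months.
- That an SD of 3 is too small. It is offered as an illustration, and the claim in SD units does not depend on it. A larger value would require assumptions about the counting period and the within-patient correlation that the document does not supply.

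**Conclusion.** The stated figure is wrong under its own conditions. With 50 enrolled and 10% lost, the probability that the 95% interval has a half-width of at most 1/3 SD is about 86%, not 95%. The result rests on approximately normal differences, a t-interval and exactly 45 evaluable patients; the variants tried at 10% loss range from about 85% to 91%.

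The 95% figure corresponds to about 50 evaluable patients. That suggests the dropout allowance is not reflected in it, but the simulation is not shown, so a reader should not conclude as fact that the allowance was left out. Nor does the figure reproduce only at exactly 50: 49 gives 94.5%.

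This is a correction of a stated number, not a defect that undermines the study. The loss of precision is from 0.333 to 0.352 SD at the 95% assurance level.

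**What to change.** Restate the assurance in the Sample size section along these lines:

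> *With 50 enrolled and 10% dropout (45 evaluable), there is about an 86% chance that the half-width of the 95% confidence interval for the mean change is at most 1/3 SD, and a 95% chance that it is at most about 0.35 SD (1.06 episodes if the SD is 3).*

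In the worked example, replace the phrase about the interval falling within the mean ± 1 with a statement that its half-width is at most 1, and give the probability for 45 evaluable patients.

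The cost is wording only, with a slightly less favourable figure and no extra patients. If the investigators prefer to keep 95% for 1/3 SD after 10% loss, 50/0.9 = 55.6, so 56 would need to be enrolled. The size of the shortfall does not by itself require this.
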